## Primary outcome measure

### Saccade frequency during gait

The primary outcome measure was saccade frequency (number of fast eye movements per second when walking) during gait, which was recorded via the Dikablis mobile eye-tracker and EOG systems.

### Secondary outcome measures

***Visual sampling.*** Secondary visual sampling outcomes included: saccade number, velocity, acceleration, amplitude and duration, as well as fixation number and duration.

***Gait characteristics.*** Gait characteristics were measured via video recording and a Vicon 3D motion capture system for all walking conditions in order to examine associations between cognitive and visual functions and gait, and saccadic frequency and gait (
Figure 1). Spatiotemporal gait characteristics included step velocity, step length, step time, single support time and double support time, which were chosen because they have been selectively associated with cognitive
^74^ and visual functions
^75,
76^ in people with PD and older adults in previous research.

***Safety considerations.*** All measurements were non-invasive and placed the participant at no risk other than those that normally may occur during walking. To prevent excessive fatigue, participants were encouraged to take breaks as needed throughout all study procedures. The hypoallergenic double-sided tape used to fix the infra-red markers and Dikablis head unit onto the skin of the participants did not cause any adverse effects. The amount of tape was small and it has been used on numerous occasions in other research projects at the CARU and no issues have been reported. The bi-temporal EOG electrodes also did not cause any adverse effects. The treadmill used within the accuracy and reliability testing was equipped with a safety harness to avoid any falls-related injuries, as the harness could support the participant and trigger the treadmill to automatically stop in the event of a fall.

***Ethical approval.*** Ethical approval for this project was obtained from the NRES Committee North East -Newcastle and North Tyneside 1 Research Ethics Committee (approved 6
^th^ June 2013, Reference 13/NE/0128). Written informed consent was obtained for every participant prior to testing. The study began 1
^st^ July 2013.

***Dissemination.*** Data collection for the study finished in July 2015 and results will be published within peer reviewed scientific journals, open-access publication will be preferred. A public engagement event will also be used to disseminate findings to participants and public. All participants were assigned participant numbers, allowing data to be anonymised and reported confidentially. All results from the study will be uploaded to Clinicaltrails.gov (ID: NCT02610634) once analysed. No contractual agreement limits access to data.

## Statistical analysis

### Sample size

This was an exploratory study and therefore few specific previous examples were available to guide estimates for sample size. We have based the estimate (≥40 participants in each group) on our previous work (PD; n=21)
^29^ and other previous similar studies. Similar studies in this research area
^72,
73,
77–
80^ have used small sample sizes (n=2–26) and reported between-group differences, demonstrating that we will be able to see differences between our sizable PD and control groups. It is a general recommendation to include 30 cases per group to be able to carry out basic statistical tests (e.g. between group comparisons)
^81^. This study will inform future power calculations.

Data analysis will follow a predetermined plan:

### Analysis common to all studies

Statistical analysis will be undertaken using SPSS version 21 (SPPS, Inc. an IBM company). Demographic characteristics and baseline data will be summarized using descriptive statistics, including means, standard deviations, median, minimum, maximum and inter-quartile ranges for continuous or ordinal data and percentages for categorical data. The descriptive statistics will be tabulated and presented graphically for clarity. One-sample Kolmogorov-Smirnov tests will be used to check for normally distributed data. Non-normally distributed continuous distributions will be transformed where appropriate to meet the requirements of parametric tests; otherwise equivalent non-parametric tests will be adopted. Data will also be assessed graphically (such as histograms or scatter plots) for clarity of information. As this is an exploratory study a threshold of
*p* < .05 (two-sided) will guide statistical interpretation. A brief summary of participant demographic and clinical outcomes is provided in
Table 3.

**Table 3. T3:** Brief summary of demographic and clinical features.

		Control (n=40) Mean (SD)	PD (n=60) Mean (SD)	***p***
Demographic	Age (years)	66.93 (10.86)	67.77 (7.60)	.649
	Sex	17M/23F	38M/22F	**.041** †
	Education (years)	14.80 (3.03)	13.28 (3.61)	**.031 ***
	Depression scale (GDS-15)	0.70 (0.88)	2.80 (2.77)	**.000 ***
	Falls efficacy scale (FES-I)	18.98 (4.15)	25.48 (8.99)	**.000 ***
Clinical	Hoehn and Yahr stage (H&Y)	-	I (21)/II (33)/III (6)	-
	Disease duration (months)	-	75.38 (75.50)	-
	UPDRS part III	-	37.13 (13.84)	-
	FOGQ	-	4.33 (7.21)	-
	LED	-	629.49 (412.82)	-

*independent t-test significance level p<.05, † = X², LED = levodopa equivalent dose, FOGQ = freezing of gait questionnaire and UPDRS III = unified Parkinson’s disease rating scale (motor subsection)

### Further analysis

Study aims will be addressed using the specific analysis provided below:

***1) To examine the independent roles of cognition and vision in gait in PD***

Associations between cognition, visual functions and gait characteristics will initially be made using Pearson correlations, which will be followed by structural equation modelling (SEM) (detailed below).

***2) To examine the interaction between cognitive and visual functions (termed visuo-cognition)***

Visual sampling (saccade frequency) is an online behavioural measure of visuo-cognition due to its known relationship with cognitive and visual functions
^82^. To analyse visual sampling during gait, a series of mixed analysis of variance (ANOVA) will be used with effect of PD (PD and control) as between participant factor and attention (single task, dual task) and environment (Straight walk, Door, Turn) as within group factors. Pearson’s correlations will be used to test the strength and direction of the relationships between clinical, gait and saccade frequency outcomes. Gait characteristics will also be assessed with the same mixed ANOVA method.

To test the effect of visual cueing on visual sampling and gait; a mixed ANOVA will be used with group (PD and control), visual cue (no cue and cue) and attention (single task, dual task). Comparison with and without a visual cue will also be made via the same mixed ANOVA for the various gait characteristics, while controlling for the influence height.

Associations between cognitive and visual functions will be made using Pearson correlations. Cognitive and visual function contribution to visual sampling will be assessed using multiple regression analysis, while controlling for demographic factors (age, motor severity, depression, global cognition). This will be performed in several steps; Step 1: Demographics, Step 2: Cognition (attention, executive function, visuo-spatial ability, working memory), Step 3: Visual functions (visual acuity, contrast sensitivity), and Step 4: Visuo-cognition (combination of all of the variables in the above steps).

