**Figure 1. f1:**
[figure not shown]
Walking conditions.

Environmental conditions included; walking straight, walking straight through a doorway and turning while walking through a doorway (see
Figure 1). The visual sampling during gait testing was also repeated with a visual cue in place for the straight walks. The visual cue consisted of transverse black tape lines on a white floor placed 50cm apart (approx. a ‘normal’ step length) as depicted in
Figure 1, which participants were asked to step over as they complete the walk. A visual cue was used as they are known to help ameliorate gait impairments in PD
^61^, which may be due to the increased task-related visual information
^62^ or greater attention being allocated to gait
^61^.

Attentional conditions included; single task (i.e. just walking) and dual task (i.e. repeating numbers while walking based on a maximal forward digit span obtained in sitting). A dual task was used as a representative of real-world walking, in which carrying out several tasks at once is common (i.e. walking and talking)
^60^.

Both groups (PD and controls) performed the same walking conditions (
Figure 1); with repeat measures (three trials for each condition) taken for an average to be created.

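### The mixed ANOVAs on condition averages use only participants with every condition; a linear mixed model on the same averages would use all available cells (minor)

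*Protocol article*

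**What the plan says.** The primary outcome is fixed in the protocol article under Primary outcome measure: "The primary outcome measure was saccade frequency (number of fast eye movements per second when walking) during gait".

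Under Further analysis, aim 2, it is to be analysed by a "series of mixed analysis of variance". Group (PD or control) is the between-participant factor, with "attention (single task, dual task) and environment (Straight walk, Door, Turn) as within group factors". A second mixed ANOVA has group, "visual cue (no cue and cue) and attention (single task, dual task"). For gait: "Gait characteristics will also be assessed with the same mixed ANOVA method". The cue comparison of gait is also adjusted for height.

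The section on measuring visual sampling during gait (with Figure 1) fixes what enters each cell. Both groups walk under the same conditions, "with repeat measures (three trials for each condition) taken for an average to be created". Each participant therefore gives one value per condition.

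Analysis common to all studies names the software: "Statistical analysis will be undertaken using SPSS version 21". It names neither the procedure nor a rule for a missing condition. The article gives no rate of unusable recordings.

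**The concern.** A classical mixed ANOVA with one value per cell compares complete profiles. If one of six condition averages cannot be formed, the other five are lost to that analysis as well. This follows from the method the article fixes, so it is more than a missing-data rule left to an analysis plan.

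Two things are at stake. The first is precision: the Sample size section aims for at least 40 per group and cites 30 per group as a general recommendation for basic tests. Exactly 40 controls were recruited, so there is no reserve in that group. The second is bias: if the chance of losing a condition depends on how a person performs, completers are a selected subset, and the selection may differ between PD and controls.

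**Working it through.** **Inputs from the article.** 60 PD and 40 controls; 2 x 3 = 6 cells for attention by environment; 2 x 2 = 4 cells for cue by attention; three trials averaged per condition. The sample size rests on precedent, with no effect size, SD or power, so there is no stated figure to reproduce.

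**Assumed input.** q is the chance that a participant has no usable average in a given condition. The article does not give it, so a range is shown.

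**Step 1: independent whole-condition losses.** Share with all k cells = (1 - q)^k.

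| q | 6 cells | PD / controls left | 4 cells | PD / controls left |
|---|---|---|---|---|
| 1% | 0.99^6 = 94% | 56.5 / 37.7 | 0.99^4 = 96% | 57.6 / 38.4 |
| 2% | 0.98^6 = 89% | 53.2 / 35.4 | 0.98^4 = 92% | 55.3 / 36.9 |
| 5% | 0.95^6 = 74% | 44.1 / 29.4 | 0.95^4 = 81% | 48.9 / 32.6 |
| 10% | 0.90^6 = 53% | 31.9 / 21.3 | 0.90^4 = 66% | 39.4 / 26.2 |

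At 5% the controls in the six-cell analysis fall just below 30.

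**Step 2: more favourable patterns.**
- *Losses fall on the same people.* The share is 1 - q, for example 95% at q = 5%. These people have no data in any condition, so a mixed model cannot recover them either.
- *Any one usable trial makes an average.* With independent trial loss t, q = t^3 and the six-cell share is (1 - t^3)^6. Trial loss of 10%, 20% or 30% leaves 99%, 95% or 85%. Reaching q = 5% needs t = 0.05^(1/3) = 37%.

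**Step 3: a less favourable pattern.** If all three trials were required, the share is (1 - t)^18: 40% at t = 5% and 15% at t = 10%. The article does not impose this rule.

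**Step 4: power, by simulation.** 300 runs per scenario; 40 v 60; six cells; assumed within-person correlation 0.6 and group effect 0.5 SD; cells lost completely at random. Power for the group effect, complete-case ANOVA v random-intercept model on cell values:
- no loss: 81% v 83%
- q = 5%: 73% v 85%
- q = 10%: 57% v 82%

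With 300 runs each figure carries an error of about 2 to 3 points. Differences of that size, including the first pair, mean nothing.

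**Step 5: bias, by simulation.** Loss was made to depend on the observed first condition and was halved in controls (base rate 10%). Against a true difference of 0.50, completers averaged 0.56 and the mixed model 0.47, with simulation error about 0.01. The completers' estimate can therefore be biased. The mixed model also missed in this run, so the case for it rests on its validity under missing at random, not on this one figure. The direction follows from the pattern assumed and says nothing about this study.

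**Step 6: why not trial-level data with only a random participant intercept.** Let the trial SD be 1 (assumed) and s the participant-by-condition SD.
- The true variance of a cell average about the participant level is (1 + 3s^2)/3.
- Per participant there are 12 within-cell degrees of freedom with variance 1, and 5 between cells with variance 1 + 3s^2. The model pools them to (12 + 5(1 + 3s^2))/17 = 1 + 15s^2/17.
- The test statistic is therefore inflated by the square root of (1 + 3s^2)/(1 + 15s^2/17).
- s = 0.5: 1.75/1.221 = 1.434, root 1.197; 1.96/1.197 = 1.64; false-positive rate about 10%.
- s = 1.0: 4/1.882 = 2.125, root 1.458; 1.96/1.458 = 1.34; about 18%.

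A simulation of group by attention under the null with complete data (4,000 runs) gave 10.8% and 17.9%. The analysis of averages stayed at 4.7% to 5.4%.

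**The case against.** The strongest reply is that nothing here is wrong: a mixed ANOVA is a standard, valid method for this design, the study is declared exploratory, and no missing condition is reported. Deletion of incomplete cases is inferred from the method, since the SPSS procedure is not named, and a rule for missing conditions may sit in an analysis plan that is not shown. Several features also limit loss: vision-specific exclusions chosen for eye-tracking, unaided walking, Hoehn and Yahr I to III (6 of 60 at stage III), rest breaks, two eye-movement recording systems, and all main conditions in one session. Deletion is also per analysis: someone lacking only a cued condition stays in the attention by environment ANOVA.

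All of this stands, and it sets the severity. It does not remove the point, because the article fixes a method that cannot use a partial profile when one that can asks the same questions.

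Three stronger readings are tempting and are not supported:
- *That dropping incomplete participants shifts the PD group towards milder cases.* The article has no data on who loses conditions, so this is conjecture.
- *That averaging three trials is itself a defect.* Averaging gives unequally measured cells equal weight, but it also protects a cell when single trials fail.
- *That any mixed model would leave complete-data results essentially unchanged.* This is false for the trial-level version with only a participant intercept, as Step 6 shows.

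**Conclusion.** The point holds as a minor, inexpensive improvement. Each planned mixed ANOVA uses only participants with all six (or four) condition averages. The resulting loss runs from nil with complete data to about a quarter of participants on six cells at an assumed, independent 5% loss per condition, and nearly half at 10%. It is much less if any usable trial yields an average or if losses cluster. Both the rate and the independence are assumptions. Bias in the group comparison is possible when loss depends on observed performance, but neither its presence nor its direction can be read from the article. No stated number is shown to be wrong.

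**What to change.** Under aim 2, replace the mixed ANOVAs by linear mixed models on the condition averages:
- the same fixed factors and all their interactions: group, attention and environment; group, cue and attention for cueing; height added in the cue analysis of gait;
- all available cells for every participant with at least one;
- an unstructured within-participant covariance with Satterthwaite degrees of freedom or, if that is too rich, random participant, participant-by-attention and participant-by-environment effects (participant-by-cue in the cue model).

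State how many usable trials make an average, and report the number of participants and cells in each analysis. Do not fit trial-level data with only a random participant intercept; if trial-level data are used, add participant-by-condition random effects.

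The cost is a change of wording, slightly more modelling work and a covariance structure to fix in advance. No new data are needed: collection has finished, and the article describes the analysis as still to come. The model assumes missing at random. It does not cure loss that depends on unobserved values, and it cannot recover people without any usable condition.

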### Participants and setting

Two groups of participants were recruited: i) People with idiopathic PD (PD) (n=60); and ii) Age-matched older adults (controls) (n=40). Inclusion criteria and exclusion criteria are highlighted in
Table 1. Vision-specific criteria (identified through medical notes) were included due to the impact of certain conditions on eye-tracking capabilities. The setting for the study was the gait laboratory at the Clinical Ageing Research Unit (CARU), Campus for Ageing and Vitality, Newcastle University, United Kingdom.

**Table 1. T1:** Inclusion and Exclusion Criteria.

Inclusion Criteria	Exclusion Criteria

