**Common to all groups** • Aged ≥50 years • Able to walk unaided • Adequate hearing (as evaluated by the whisper test; stand 2m behind participant and whisper a 2 syllable word, participant repeats word) and vision capabilities (as measured using a Snellen chart – 6/18–6/12). • Stable medication for the past 1 month and anticipated over a period of 6 months **Group Specific Criteria** **Participants with PD:** • Diagnosis of idiopathic PD, as defined by the UK Brain Bank criteria ^31^ • Hoehn and Yahr stage I–III ^32^ • Stable medication for past 1 month and anticipated over next 6 months or stable Deep Brain Stimulation for at least one month and expected following 6 months • Score ≥21/30 on Montreal cognitive assessment (MoCA) which is used to classify non-demented PD (PD dementia is <21/30) ^33– 35^ • Free from any neurological disorders that may have caused cognitive impairment • No restriction was made for medication usage and participants on stable doses of medication or treatment were permitted.	**Common to all groups** • Psychiatric co-morbidity (e.g., major depressive disorder as determined by geriatric depression scale (GDS-15); >10/15 ^36^) • Clinical diagnosis of dementia or other severe cognitive impairment (PD = MoCA <21/30, Controls = MoCA <26/30 ^37^) • History of stroke, traumatic brain injury or other neurological disorders (other than PD, for that group) • Acute lower back or lower extremity pain, peripheral neuropathy, rheumatic and orthopaedic diseases • Unstable medical condition including cardio-vascular instability in the past 6 months • Unable to comply with the testing protocol or currently participating in another interfering research project • Interfering therapy **Vision Specific Criteria** • Any pupillary diameter disorder; such as significantly non-round pupils, Adies pupil (tonic or dilated pupil), Argyll- Robertson pupil (absence of light reaction), unilateral small pupil • Neuromotility disorders, such as Nystagmus or other ocular oscillations • Significant left eye disorders (i.e. squint, twitching, Ptosis [drooping eyelids]) • Known significant visual field deficits; such as hemianopia • Optic nerve disease • Optic disc elevation • Optic disc swelling; such as Papilledema or Papillitis

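### The PD-versus-control mixed ANOVAs carry no sex or education covariate despite the imbalance in Table 3, and height enters only one of the two gait ANOVAs, so the group main effect is open to confounding

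*Protocol article*

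**What the plan says.** All the models are in the Protocol article, Further analysis, aim 2.

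- **Saccade frequency (primary outcome):** a "mixed analysis of variance (ANOVA) will be used with effect of PD (PD and control) as between participant factor". The within-person factors are attention (single, dual task) and environment (straight, door, turn). No covariate is named.
- **Gait, same conditions:** "Gait characteristics will also be assessed with the same mixed ANOVA method". Again no covariate is named.
- **Visual cue, visual sampling:** "a mixed ANOVA will be used with group (PD and control), visual cue (no cue and cue) and attention (single task, dual task"). No covariate is named.
- **Visual cue, gait:** the cue comparison is repeated "for the various gait characteristics, while controlling for the influence height". This is the only ANOVA with a covariate.
- **Multiple regression on visual sampling:** done "while controlling for demographic factors (age, motor severity, depression, global cognition"). Sex and education are not in the list. The structural equation model under aim 3 reuses the regression's observed variables.

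Participants and setting describes the controls as matched on age. Table 3 marks sex (17M/23F against 38M/22F, p = .041) and education (14.80 against 13.28 years, p = .031) as different between the groups. Dissemination says data collection ended in July 2015, while the analysis is still written in the future tense.

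**The concern.** This is an observational comparison of two separately recruited groups. PD participants came from a movement disorders clinic; controls came through posters and university email. Matching covered age alone, so differences in other traits pass straight into the between-group main effect, which the article names as the effect of PD.

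The article does choose covariates model by model: four in the regression, height in one gait ANOVA, none in the others. So this is not merely a detail left to a fuller plan. The models are stated, and they are stated inconsistently. Sex and education are the two background variables that its own table flags, and they appear in no model it describes. Step length and step velocity are analysed in both gait ANOVAs, but stature is allowed for in only one.

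At stake is whether a group difference in saccade frequency or gait can be read as due to PD. Sample size says the study will inform later power calculations, so a biased group effect would carry forward.

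**Working it through.** **Inputs from Table 3.** Controls n = 40, PD n = 60. Men 17/40 and 38/60. Education 14.80 (SD 3.03) and 13.28 (SD 3.61) years.

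**1. The article's own figures.**
- Education: pooled SD = √[(39 × 3.03² + 59 × 3.61²)/98] = 3.39. Then t = 1.52/(3.39 × √(1/40 + 1/60)) = 2.20, p = .030. The stated .031 agrees within rounding of the inputs. Standardised gap = 1.52/3.39 = 0.448 SD.
- Sex: 63.3% − 42.5% = 20.8 points. Pearson chi-square = 4.21, p = .040; the N−1 form gives 4.17, p = .041, the stated value. With Yates' correction p = .065 and by Fisher's test .064, so its significance depends on the variant. The argument rests on the size of the gap, not on the p-value.
- Age: p = .650 (stated .649), a gap of 0.09 SD. The age matching worked.

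**2. Bias from leaving both out.** In within-group SD units of the outcome, for a participant's average over conditions:

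bias = 0.208 × (sex effect) ± 0.448 × (education correlation)

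The sign is plus if the two imbalances push the group contrast the same way and minus if they oppose. **Assumed, not in the article:** sex effect 0.3 to 0.5 SD, education correlation 0.2 to 0.3, the two unrelated within group. The standard error of the group contrast is √(1/40 + 1/60) = 0.204 SD. The false-positive rate comes from the noncentral t with 98 df at two-sided 5% and a true PD effect of zero.

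| Sex effect | Education r | Same direction: bias, rate | Opposite: bias, rate |
|---|---|---|---|
| 0.3 | 0.2 | 0.152, 11.4% | −0.027, 5.2% |
| 0.3 | 0.3 | 0.197, 15.9% | −0.072, 6.4% |
| 0.5 | 0.2 | 0.194, 15.6% | 0.015, 5.1% |
| 0.5 | 0.3 | 0.239, 21.2% | −0.030, 5.2% |

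Sex alone gives 6% to 8%; education alone gives 7% to 10%.

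**3. Scale.** With 60 against 40, the difference detectable at 80% power is 0.578 SD. The largest bias above is 0.239/0.578 = 41% of it.

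**4. Effect of adjusting.** In 4,000 simulated data sets (sex 0.5 SD, education 0.3, same direction), the unadjusted contrast had bias 0.24 SD and a false-positive rate of 18.6%. This is a little below the 21.2% above, partly because the sex effect also adds to the outcome's variance (standard error 0.210). With sex and education as covariates, the bias was about 0 and the rate 5.7%. When neither covariate mattered, the standard error went from 0.203 to 0.213, a ratio of 1.05.

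**5. Height.** Neither Table 3 nor the rest of the article reports height by group, so no figure can be put on this part. It rests on comparing the two gait models.

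**The case against.** **No association is shown.** Confounding needs sex or education to affect the outcome, and the article gives no such association. This stands: the group effect is open to confounding, not shown to be confounded. A reader might infer an 11% to 21% error rate, but that holds only if both effects act in the same direction, which the article cannot settle.

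**Scope.** The three main aims concern cognition, vision and gait in PD, and much of each ANOVA tests within-person conditions. Sex, education and stature are fixed within a person, so they do not confound those main effects. They reach the group-by-condition interactions only if they modify a condition effect. This stands and confines the point mainly to the group main effect.

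**Height has a reason in the cue model.** The cue lines are 50 cm apart for everyone, so stature affects how demanding the cued step is. That explains including height there. It does not explain leaving it out of the other model of the same step characteristics. That height differs by group is only an inference from the sex mix.

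**Stronger readings.** A reader might infer that the unequal cognitive cut-offs ("PD = MoCA <21/30, Controls = MoCA <26/30") are a further bias, to be met by restricting PD to the control cut-off. The article uses them deliberately to define non-demented PD and unimpaired controls. Lower cognition may be a consequence of PD, so the restriction would condition on part of what is being studied. A reader might also fear that uncentred height would spoil the cue test; nothing says height is entered that way, and such coding belongs to a fuller plan.

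**Exploratory study, data already collected.** Adding covariates after seeing the imbalance is a late change, and the 5% threshold only guides interpretation. Both lower the severity. Neither removes bias, and showing both estimates answers the first.

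**Conclusion.** The point holds for the group main effect. The between-group ANOVAs for saccade frequency and gait, as written, leave out two traits on which the groups visibly differ: 20.8 percentage points in sex and 0.45 SD in education. Under the assumed associations, the spurious PD effect lies between about −0.07 and 0.24 SD, and the false-positive rate between about 5% and 21%. Those ranges depend on the assumed strengths, on the two acting independently, and on their unknown direction.

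The gait models also treat height differently without a stated reason for the difference. The article does not support saying that a group difference cannot be due to PD, or that the attention, environment or cue main effects are compromised. For an exploratory study this is a worthwhile correction to the analysis and not a fatal flaw.

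**What to change.** - Add sex and education, with age if wished, as covariates in every PD-versus-control mixed ANOVA.
- Add height to the attention-by-environment gait ANOVA, as in the cue gait ANOVA.
- Report adjusted and unadjusted group effects side by side, state that the covariates were added after Table 3 was known, and base any attribution of a group difference to PD on the adjusted estimate.
- Leave depression (GDS-15) and fear of falling (FES-I) out of this adjustment. They differ strongly between groups but may be consequences of PD.

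**Cost.** A change of wording and a rerun. Sex, education and age are already in Table 3, and the plan already relies on height. It uses 2 to 4 of about 98 degrees of freedom. If sex and education turn out not to matter, the standard error of the group effect is about 5% larger.

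### Height-adjusted cue ANOVA for gait: state that height is mean-centred, because uncentred height in SPSS GLM Repeated Measures makes the cue and attention F tests refer to a height of zero

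*Protocol article*

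**What the plan says.** The Protocol article, under aim 2 of Further analysis, tests cueing as follows: "a mixed ANOVA will be used with group (PD and control), visual cue (no cue and cue) and attention (single task, dual task"). For gait, the comparison with and without a cue is made "via the same mixed ANOVA for the various gait characteristics, while controlling for the influence height".

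Under Analysis common to all studies, the software is fixed ("Statistical analysis will be undertaken using SPSS version 21") and the criterion is p < .05 ("two-sided) will guide statistical interpretation").

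The groups are "People with idiopathic PD (PD) (n=60); and ii) Age-matched older adults (controls) (n=40"). The cue is the same for everyone: "transverse black tape lines on a white floor placed 50cm apart".

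The article does not name the SPSS procedure. It does not say whether height is centred, whether height is crossed with cue and attention, or whether the cue result is read from the F table or from marginal means.

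**The concern.** Each participant walks with and without the cue, and height is identical in both conditions. Adjusting for height therefore removes no bias from the cue contrast. Height has two useful roles in this model: in the comparison between groups, and as a possible moderator of the cue response.

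A mixed ANOVA with a person-level covariate is ordinarily run in SPSS as GLM Repeated Measures. That procedure automatically crosses the covariate with every within-person effect. The F test printed for cue is then the intercept of a regression of the person's cue difference on group and height, so it is the cue effect where height equals zero. The same holds for attention and for cue x attention. A reader would take the printed line as the cue effect at typical height.

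Two errors are possible. A real average cue effect can be missed because the extrapolation to zero is so imprecise. Or a cue response that varies with height can appear as an average cue effect when there is none. Some variation with height is plausible, because one fixed line spacing is a different demand for short and tall people.

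**Working it through.** The article gives no effect size, SD or power for this analysis, and its sample size rests on precedent ("We have based the estimate (≥40 participants in each group) on our previous work (PD; n=21")). There is no planned figure to reproduce.

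**Inputs from the article.** 60 PD and 40 controls; two levels each of cue and attention; alpha 0.05 two-sided; SPSS.

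**Inputs assumed.** Mean height 165-170 cm and SD 8-11 cm; SD of each person's cue difference set to 1.

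**Model.** For person i, let D be mean gait with cue minus mean gait without cue. GLM Repeated Measures with height is equivalent to

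D = a + b x group (effect-coded) + c x height + error,

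and the cue F test is the test of a = 0.

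**Step 1, standard error.** Moving the reference point from mean height to zero multiplies the standard error of a by about sqrt(1 + (mean/SD)^2):

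| Mean / SD (cm) | Ratio |
|---|---|
| 170 / 11 | 15.5 |
| 170 / 9.5 | 17.9 |
| 165 / 8 | 20.6 |

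Allowing for the 60/40 split changes this little. At 170/9.5, the standard error at mean height is sqrt(0.25 x (1/40 + 1/60)) = 0.102. At height zero it is sqrt(0.0104 + (170/9.5)^2/100) = 1.79, a ratio of 17.6.

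**Step 2, a real effect missed.** Take an average cue effect of 0.5 SD, unrelated to height, at 170/9.5. Centred: 0.5/0.102 = 4.90, power over 99%. Uncentred: 0.5/1.79 = 0.28, power about 6%. Simulation of 2,000 data sets agrees: 99.9% centred, 6.0% uncentred. For an effect of 1 SD the simulation gives 100% against 9.7%.

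**Step 3, a slope mistaken for an effect.** Take no cue effect at mean height and a correlation of -0.3 between cue difference and height. The fitted effect at height zero is 0.3 x 170/9.5 = 5.37 SD. Its standard error is sqrt(1 - 0.09) x 1.79 = 1.71, so the ratio is 3.14 and the test rejects about 87% of the time. Simulation gives 86.6% uncentred and 6.9% centred.

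**Step 4, sensitivity to the assumptions.** A second simulation used heights of 170/9, 165/7 and 172/11 (ratios 18.9, 23.6 and 15.7). With a cue effect of 0.33 SD, power was 0.88-0.90 centred and 0.04-0.06 uncentred. With no effect at mean height and a slope of 0.3 SD per SD of height, rejection was 0.06-0.07 centred and 0.82-0.83 uncentred.

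**Step 5, what does and does not change.** One simulated 2 x 2 x 2 data set (height 170/9):

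| Test | F, centred | F, uncentred |
|---|---|---|
| Cue | 19.84 | 1.71 |
| Attention | 13.04 | 0.17 |
| Cue x attention | 0.44 | 0.74 |
| Group x cue | 4.26 | 4.26 |
| Group x attention | 0.45 | 0.45 |
| Group x cue x attention | 4.32 | 4.32 |
| Group | 6.50 | 6.50 |

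The cue contrast evaluated at mean height from the uncentred fit, which is what marginal means report, was 2.42 with F 19.84, the same as the centred model. If height enters as a main effect only, as SPSS MIXED allows, the cue and attention tests do not depend on centring.

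**The case against.** A reader might infer that the plan, as written, tests the cue effect at height zero and so gives the wrong answer. The documents do not support that. Nothing in the article says that height is uncentred, that GLM Repeated Measures is used, or that the result is read from the F table. Centring is also a detail that an article may leave to a fuller analysis plan, which is not shown. Centring, height as a main effect only, or marginal means at mean height would each avoid the problem.

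The reach is also limited. Whether PD and control participants respond differently to the cue is untouched. The height adjustment is attached to gait characteristics, which are secondary outcomes, and not to saccade frequency. Attention effects on gait are also tested in the group x attention x environment ANOVA, where no height term is named. The cueing paragraph can even be read as an unadjusted gait analysis plus an adjusted one. The study is exploratory, and every size above rests on assumed heights and assumed cue effects.

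All of this stands, and it rules out calling the plan wrong. What remains is that the article itself chose the model, the covariate and the software, and the ordinary way of running that combination gives misleading within-person tests unless height is centred. The adjustment brings no protection against confounding of the cue contrast in return.

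**Conclusion.** The point holds as a conditional one. If height is entered uncentred in SPSS GLM Repeated Measures, the cue, attention and cue x attention F tests in the height-adjusted gait ANOVA refer to a height of zero. Their standard errors are then about 15 to 21 times those at mean height, assuming mean height 165-170 cm and SD 8-11 cm. Under that condition a large cue effect can be missed, and a cue-by-height slope can be read as an average effect. How far this would alter the trial's results cannot be said, because the article gives neither the heights nor the implementation. All group-related results and the primary outcome are safe either way. This is a free improvement and not an established error.

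**What to change.** Add one sentence to the cueing analysis: in the height-adjusted gait ANOVA, height is entered as height minus the sample mean, so that the cue, attention and cue x attention tests refer to a participant of average height.

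Alternatively, take those three within-person tests from the model without height, and report cue x height separately as a moderator.

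The cost is one computed variable and one sentence. No new data are needed, and the tests involving group are the same with centred or uncentred height.
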